## Abstract

**Background:**

Community-acquired pneumonia (CAP) is a significant public health concern and a leading cause of hospitalization and inpatient antimicrobial use in the USA. However, determining the etiologic pathogen is challenging because traditional culture methods are slow and insensitive, leading to prolonged empiric therapy with extended-spectrum antibiotics (ESA) that contributes to increased hospital length of stay, and antimicrobial resistance. Two potential ways to reduce the exposure to ESA are (a) rapid diagnostic assays that can provide accurate results within hours, obviating the need for empiric therapy, and (b) de-escalation following negative bacterial cultures in clinically stable patients.

**Methods:**

We will conduct a large pragmatic 2 × 2 factorial cluster-randomized controlled trial across 12 hospitals in the Cleveland Clinic Health System that will test these two approaches to reducing the use of ESA in adult patients (age ≥ 18 years) with CAP. We will enroll over 12,000 patients and evaluate the independent and combined effects of routine use of rapid diagnostic testing at admission and pharmacist-led de-escalation after 48 h for clinically stable patients with negative cultures vs usual care. We hypothesize that both approaches will reduce days on ESA. Our primary outcome is the duration of exposure to ESA therapy, a key driver of antimicrobial resistance. Secondary outcomes include detection of respiratory viruses, treatment with anti-viral medications, positive pneumococcal urinary antigen test, de-escalation by 72 h from admission, re-escalation to ESA after de-escalation, total duration of any antibiotic, 14-day in-hospital mortality, intensive care unit transfer after admission, healthcare-associated *C. difficile* infection, acute kidney injury, total inpatient cost, and hospital length-of-stay.

**Discussion:**

Our study aims to determine whether identifying an etiological agent early and pharmacist-led de-escalation (calling attention to negative cultures) can safely reduce the use of ESA in patients with CAP. If successful, our findings should lead to better antimicrobial stewardship, as well as improved patient outcomes and reduced healthcare costs. Our findings may also inform clinical guidelines on the optimal management of CAP.

**Trial registration:**

ClinicalTrials.gov NCT05568654. Registered on October 4, 2022.

**Supplementary Information:**

The online version contains supplementary material available at 10.1186/s13063-023-07615-3.

## Introduction

### Background and rationale

Community-acquired pneumonia (CAP) is a significant cause of morbidity and mortality, resulting in > 1.7 million adult hospitalizations annually, making it the second most common cause of hospitalization in the USA [1–3]. One contributing factor to the overuse of extended-spectrum antibiotics (ESA) for CAP is that the causative pathogen is unknown in nearly half of cases, and initial treatment is almost always empiric [4, 5]. Guidelines of the American Thoracic Society and Infectious Diseases Society of America (ATS/IDSA) recommend limiting ESA to inpatients with risk factors for resistant pathogens, but many inpatients with CAP receive ESA, often throughout their hospital stay [6–8].

An accurate pathogenic diagnosis can contribute to antimicrobial stewardship in 2 ways: (1) by allowing for initial narrow-spectrum therapy and (2) by providing confidence when de-escalating therapy following negative cultures. However, without a diagnostic test, many clinicians are uncomfortable with de-escalation, fearing an undiagnosed resistant pathogen could cause treatment failure. Rapid molecular diagnostic assays have the potential to identify causative pathogens, but they are rarely part of the diagnostic work-up, and results are often ignored [9, 10]. In a national sample of patients with CAP from 177 US hospitals, we found that only 16% had a pneumococcal urinary antigen testing (UAT) performed and < 25% were tested for respiratory viruses [11, 12]. Both the ATS/IDSA CAP guidelines and the antimicrobial stewardship implementation guidelines recommend routine testing of inpatients for influenza during influenza activity; neither one recommends routine UAT testing [6, 13]. Both sets of recommendations are based on limited evidence and it is not known whether widespread testing for viruses would reduce antibiotic use. In a multi-hospital dataset, we found that patients who tested positive for respiratory viruses received 0.8 fewer days of antibiotics, and patients who tested positive with UAT were twice as likely to have their ESA de-escalated by hospital day 3 [11, 12]. There is therefore a need for large, randomized trials that can evaluate the impact of initial diagnostic testing on antibiotic prescribing and patient outcomes.

De-escalation following negative bacterial cultures is another antimicrobial stewardship target. While most de-escalation follows the identification of a susceptible pathogen, the IDSA/ATS guidelines also recommend de-escalation to a narrower spectrum at 48 h if cultures are negative [6]. However, this recommendation is based on observational studies. In our study of 164 US hospitals, we found that de-escalation practices following negative cultures varied widely by hospital, and no hospital de-escalated even 40% of eligible patients [14]. De-escalation was associated with shorter length of stay and lower rates of inpatient mortality. A hospital-wide pharmacist-led effort to encourage physicians to follow the ATS/IDSA guidelines and de-escalate after 48 h could help overcome fears about resistant pathogens and treatment failure.

### Objectives and study aims

This large, multicenter 2 × 2 factorial cluster-randomized controlled trial aims to reduce ESA use in patients with CAP by optimizing rapid pathogen detection and improving de-escalation rates following negative cultures. The study has two aims:

Aim 1: To determine the impact of comprehensive pneumococcal UAT and rapid viral molecular diagnostic assays on antimicrobial prescribing for CAP.Hypothesis 1: Comprehensive diagnostic testing will allow fewer days of ESA.Aim 2: To compare pharmacist-led de-escalation of empiric antimicrobial therapy following negative cultures to usual care.Hypothesis 2a: Pharmacist-led de-escalation will reduce the number of days of ESA use.Hypothesis 2b: Pharmacist-led de-escalation will be more effective when physicians order UAT/rapid viral testing.

The study proposal was designed following the recommendations of the Standard Protocol Items: Recommendations for Interventional Trials (SPIRIT) and their checklist is included as an Additional file [15].

### Trial design

We will perform a pragmatic, multicenter 2 × 2 factorial cluster-randomized controlled trial with four arms: rapid diagnostic testing, pharmacist-led de-escalation, rapid diagnostic testing + pharmacist-led de-escalation, and usual care (Table 1).

**Table 1 Tab1:** Two-by-two factorial cluster-randomized controlled trial with four arms

		Pharmacist-led de-escalation	
		Yes	No
Rapid diagnostic testing	Yes	Rapid diagnostic testing + pharmacist-led de-escalation (3 hospitals)	Rapid testing (3 hospitals)
	No	Pharmacist-led de-escalation (3 hospitals)	Usual care (3 hospitals)

We hypothesize there will be an interaction between the two interventions as the diagnostic tests should make it easier for the pharmacist to recommend to clinicians to de-escalate after 48 h. The factorial design allows for comparing the two interventions in combination and individually, against the standard of care. All interventions will be performed at the hospital level to minimize crossover between study arms and allow for consistent care. We will use a cluster-randomized design to minimize cross-contamination and improve the efficiency of intervention administration.

## Methods: participants, interventions, and outcomes

### Study setting

The Cleveland Clinic is an integrated health system with over 51,000 clinicians and 6000 beds, consisting of 11 regional hospitals in Ohio and 5 in Florida. We identified 12 hospitals (2 large academic medical centers and 10 community hospitals) within the Cleveland Clinic Health System (CCHS) for participation based on the number of annual CAP admissions, teaching status, staffing by the Department of Hospital Medicine, antimicrobial stewardship programs, and hospital size.

### Participating sites

Enrolling sites will include ten hospitals in Northeast Ohio (Cleveland Clinic Main Campus, Fairview Hospital, Hillcrest Hospital, Marymount Hospital, Akron General Hospital, Avon Hospital, Euclid Hospital, Lutheran Hospital, Medina Hospital, and South Pointe Hospital) and two from Florida (Weston and Indian River Hospital) (Table 2). Hospitals will be divided into 3 strata based on teaching status, size of the hospital, and number of CAP patients with each stratum containing 4 hospitals. The hospitals will then be randomized to each of the 4 trial arms with an effective sample size of 3 hospitals in each arm.

**Table 2 Tab2:** Enrolling hospital sites by bed size and teaching status

Hospital	Number of beds	Residency program
Cleveland Clinic Main Campus	1167	Yes
Fairview General Hospital	488	Yes
Hillcrest Hospital	341	No
Marymount Hospital	195	No
Akron General	532	Yes
Avon Hospital	126	No
Euclid Hospital	110	No
Lutheran Hospital	119	Yes
Medina Hospital	148	No
South Pointe Hospital	167	Yes
Cleveland Clinic Florida, Weston Hospital	230	Yes
Indian River Hospital	332	No

### Eligibility criteria

The inclusion criteria for patient records are as follows:Men or women aged 18 years or olderAdmitted to a participating (i.e., enrolled and randomized) hospitalAdmitting diagnosis of pneumonia

The exclusion criteria are as follows:Admission to the intensive care unit (ICU) within 24 h of hospital admissionComfort care measures onlyCystic fibrosis (ICD10 codes present on admission)Discharged from an acute care hospital in the past weekPatients not eligible for empiric therapy due to a known pathogen (any positive blood or respiratory cultures in the 72 h prior to admission)

### Study recruitment and participant identification

All CCHS hospitals utilize the same Electronic Medical Record (EMR) system which includes an EMR-based clinical decision support system (CDSS). When the emergency department (ED) provider admits a patient age 18 years or older to a medical floor (i.e., non-ICU bed) with an admitting diagnosis of pneumonia, the pneumonia admission order set is triggered. If the physician is in a hospital randomized to the rapid diagnostic testing arm, a CDSS-based alert will be generated in real time, and the form will append orders for diagnostic testing. Initially, this will consist of urinary antigen testing for Streptococcus, but other diagnostic tests may be added later, depending on availability and local policies. For physicians at a hospital randomized to the control condition, ordering will proceed as usual (standard-of-care). They may order any diagnostic test, but none are suggested or appended. Another algorithm will help identify study patients who have negative culture results (blood and/or respiratory) for greater than 48 h and generate a list for the antimicrobial stewardship pharmacist, who will be a member of the study team. The alerts will be audited by the pharmacist daily on weekdays at a centralized location. In clinically stable patients from hospitals randomized to the de-escalation arm, the pharmacist will communicate their recommendations for de-escalation to the clinical providers via secure electronic medical record chat, phone call, or page.

### Who will take informed consent?

The study is a low-risk quality-improvement initiative performed at the hospital level, making it impractical for patients to opt out of the study. We have obtained approval from the Cleveland Clinic Institutional Review Board for a waiver of informed consent. The interventions are considered minimal risk because physicians can override the orders for rapid diagnostic testing and pharmacist recommendations for de-escalation, with final decisions depending on the individual physician’s judgment. All research will be conducted in accordance with the Declaration of Helsinki and the guidelines for Good Clinical Practice.

### Interventions

The study will evaluate (a) routine use of rapid diagnostic testing at the time of admission, (b) pharmacist-led de-escalation after 48 h for clinically stable patients with negative cultures, and c) the interaction between the two.

### Delivery of interventions

#### Rapid diagnostic testing

Eligible patients at hospitals randomized to this arm will undergo testing for viral pathogens (from November to April) and pneumococcal UAT testing. Legionella UAT was not selected as a diagnostic test as Legionella accounts for ~ 1.5% of CAP. For non-ICU admitted patients with a pneumonia diagnosis, the CDSS form will append orders for viral and UAT testing in hospitals randomized to the intervention. Providers in the intervention group will see pre-populated orders for rapid diagnostic testing but can cancel one or both orders if they so choose.

#### Pharmacist-led de-escalation

Another algorithm will identify CAP patients meeting study criteria with negative culture results for more than 48 h, generating a list for the clinical pharmacist. The pharmacist will audit the daily alerts on weekdays at a centralized location and assess patient clinical stability using the 2019 ATS/IDSA criteria for clinical stability:A.Resolved vital sign abnormalities (temperature ≤ 37.8 °C, heart rate ≤ 100 beats/min, arterial oxygen saturation ≥ 90% or pO_2_ ≥ 60 mmHg on room air, systolic blood pressure ≥ 90 mmHg, and respiratory rate ≤ 24 breaths/min),B.Normal mental status (as deemed by the clinician), andC.Ability to maintain oral intake [6].

For clinically stable patients, the pharmacist will recommend antimicrobial de-escalation to clinical providers via secure electronic medical record chat, phone call, or page. De-escalation in this context means stopping all ESA agents (anti-MRSA/anti-pseudomonal) but continuing other antibiotics. The pharmacist’s recommendations will be based on a protocol developed by the Cleveland Clinic Health System’s Antimicrobial Stewardship committee, outlining four possible clinical scenarios: (a) positive culture, (b) negative culture, (c) pneumococcal UAT results, and (d) viral test results.

Pharmacist-led de-escalation efforts will be supported by educational initiatives targeting hospitalists, including presentations about the study and audit-and-feedback for adherence to pharmacist recommendations. Site champions at each hospital will ensure intervention fidelity and encourage physician receptiveness to pharmacist messages/calls.

### Control

Control hospital patients will receive usual care, without specific CDSS alerts and pharmacist-led de-escalation efforts.

### Outcomes

The primary outcome is the duration of exposure to ESA therapy defined by the number of days of antibiotic therapy in the first 21 days of admission, following the National Healthcare Safety Network (NHSN) guidelines. ESA therapy for CAP will be defined as drugs that cover MRSA and Pseudomonas and are on Cleveland Clinic formulary (imipenem, meropenem, piperacillin-tazobactam, aztreonam, cefepime, ceftazidime, tobramycin, ceftazidime-avibactam, ceftolozane-tazobactam, meropenem-vaborbactam, imipenem-cilastatin-relebactam, cefiderocol, ceftaroline, tigecycline, eravacycline, amikacin, linezolid, or vancomycin). Any re-escalation of ESA will be counted towards the total duration of therapy. If two ESAs are administered on the same day, that will count as 2 antibiotic days. For antibiotics that are administered more than once daily, we will follow NHSN guidelines counting multiple doses of the same drug as a single antibiotic day. The duration of therapy for patients who receive a portion of their antimicrobial therapy outside the hospital will be calculated based on documented doses in the EHR and expected doses outlined in the discharge medication list, including IV and PO doses as prescribed.

Secondary outcomes:Within 48 h of admission:Viral testing ordered (yes/no): Proportion of patients for whom viral testing was ordered. We will analyze each virus individually as well as all viruses combined (i.e., any viral testing).Proportion of patients testing positive for influenza within 48 hDetection of RSV (yes/no): Proportion of patients testing positive for RSVDetection of viruses/other CAP pathogens (yes/no): Proportion of patients testing positive for each of the viruses/other CAP pathogensTreatment with anti-viral medications (oseltamivir, zanamivir, peramivir, baloxavir, ribavirin, remdesivir, nirmatrelvir, COVID-19 medications) (yes/no)Proportion of patients for whom *S. pneumoniae* urinary antigen test (UAT) is performed.Proportion of patients with a positive pneumococcal UAT.Treatment with antiviral medications (oseltamivir, zanamivir, peramivir, baloxavir, ribavirin, remdesivir, nirmatrelvir, COVID-19 medications) within 21 daysDe-escalation of ESA within 72 h from admission (yes/no) — Proportion of patients whose ESA (imipenem, meropenem, piperacillin-tazobactam, aztreonam, cefepime, ceftazidime, tobramycin, ceftazidime-avibactam, ceftolozane-tazobactam, meropenem-vaborbactam, imipenem-cilastatin-relebactam, cefiderocol, ceftaroline, tigecycline, eravacycline, amikacin, linezolid, or vancomycin) are de-escalated within 72 h from admission.Re-escalation to ESA after de-escalation (yes/no) within 21 days from admission. Proportion of patients whose antibiotics were de-escalated and that were subsequently re-escalated to ESA (imipenem, meropenem, piperacillin-tazobactam, aztreonam, cefepime, ceftazidime, tobramycin, linezolid or vancomycin).Total duration of any antibacterial antibiotic within 21 days. Total duration of any antibacterial antibiotic treatment up to 21 days, including re-initiation of antibiotics.Fourteen-day mortality. Patient’s vital status will be ascertained from the EHR if available, otherwise from the Ohio State Death Index.Thirty-day mortality.ICU transfer after admission (> 24 h after admission): Proportion of patients transferred to the ICU > 24 h after admission up to 21 days.Healthcare-associated *Clostridioides difficile* infection (CDI) (yes/no) — CDI after 72 h of admission: Proportion of patients with CDI after 72 h of admission until 30 days.Acute kidney injury (AKI) after 48 h within 21 days (yes/no): Proportion of patients with AKI after 48 h of admission. AKI will be defined as an increase in serum creatinine ≥ 0.3 mg/dl within 48 h or an increase > 1.5 times baseline [16].Total inpatient cost (from the hospital’s cost accounting system): From admission to discharge or 21 days, whichever comes first.Hospital length-of-stay (days, hours) — length of stay will be calculated as whole days from the time of admission to the time of discharge.Empyema (yes/no) — after 48 h, within 21 daysThirty-day readmission (yes/no)Infection with a resistant organism in the future (yes/no) within 6 months after discharge. Resistance to CAP therapy will be defined as resistance to either a respiratory quinolone or to both a beta-lactam/3rd generation cephalosporin and a macrolide. Multi-drug resistance will be defined as any CAP bacterial isolate that tests either intermediate (I) or resistant (R) to at least one agent in three or more antimicrobial classes.

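### Re-escalation is scored on 9 of the 18 agents that define ESA elsewhere in the protocol; separately, no death source is named for the two Florida hospitals

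*Protocol article*

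**What the plan says.** **Re-escalation.** The Outcomes section of the protocol article sets the ESA definition for the primary outcome: "ESA therapy for CAP will be defined as drugs that cover MRSA and Pseudomonas and are on Cleveland Clinic formulary". A list of agents follows, ending "ceftazidime-avibactam, ceftolozane-tazobactam, meropenem-vaborbactam, imipenem-cilastatin-relebactam, cefiderocol, ceftaroline, tigecycline, eravacycline, amikacin, linezolid, or vancomycin". On restarts it says: "Any re-escalation of ESA will be counted towards the total duration of therapy". Among the secondary outcomes, de-escalation repeats the same list, ending "meropenem-vaborbactam, imipenem-cilastatin-relebactam, cefiderocol, ceftaroline, tigecycline, eravacycline, amikacin, linezolid, or vancomycin) are de-escalated within 72 h from admission". The next outcome, re-escalation within 21 days, is the "Proportion of patients whose antibiotics were de-escalated and that were subsequently re-escalated to ESA (imipenem, meropenem, piperacillin-tazobactam, aztreonam, cefepime, ceftazidime, tobramycin, linezolid or vancomycin".

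**Mortality.** For 14-day mortality, the Outcomes section says that "vital status will be ascertained from the EHR if available, otherwise from the Ohio State Death Index". Thirty-day mortality is listed next, with no source of its own. The Discussion lists the EHR, the Ohio index or other registries held by the health system. Participating sites names ten hospitals in Northeast Ohio "and two from Florida (Weston and Indian River Hospital". The abstract gives the outcome as "14-day in-hospital mortality".

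Thirty-day all-cause death is also the measure in the six-monthly safety comparison (Interim analyses) and in the four-group comparison that must precede the primary analysis (Data analysis plan).

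**The concern.** De-escalation and its reversal are meant to be two sides of one measure. If stopping is scored on 18 agents and restarting on nine, some reversals drop out and de-escalation looks more durable than it was. The primary outcome would disagree with the secondary one for the same patient, since it counts ESA days on all 18.

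For mortality, the only external death index named covers one state, while two whole clusters are in another. The hospital is the unit of randomization, so any shortfall in recorded deaths at a Florida site falls on the single arm that holds it. The article says it hopes to demonstrate that de-escalation is safe, and 30-day death is its safety-monitoring measure.

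**Working it through.** **1. The agent lists, from the Outcomes section.**

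| Outcome | Agents named |
|---|---|
| Primary: days of ESA | 18 |
| De-escalation within 72 h | 18 (same list) |
| Re-escalation within 21 days | 9 |

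All nine agents in the short list appear in the long one, so 18 − 9 = 9 are omitted. In alphabetical order they are amikacin, cefiderocol, ceftaroline, ceftazidime-avibactam, ceftolozane-tazobactam, eravacycline, imipenem-cilastatin-relebactam, meropenem-vaborbactam and tigecycline.

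**2. What the short list does to one patient.** Take a patient whose ESA is stopped within 72 h and who later receives ceftaroline alone.

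- Primary outcome: the ceftaroline days count.
- De-escalation: yes.
- Re-escalation, read literally: no.

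If the restart also includes any of the nine listed agents, such as vancomycin, the event is captured. Only restarts made solely of omitted agents are lost.

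**3. Direction.** The short list is a subset of the long one, so each arm's re-escalation proportion can only be equal or lower under it. Let q be the share of true re-escalations made solely on omitted agents. The observed proportion is then (1 − q) × true proportion. If q is the same in all arms, differences between arms shrink by the same factor. The documents give no figure for q, so the number of lost events cannot be calculated.

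**4. Florida share, from Table 2.** Hospitals: 2/12 = 16.7%. Beds: (230 + 332)/3955 = 562/3955 = 14.2%.

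**5. Spread over arms.** There are four arms of three hospitals. Two Florida hospitals can occupy at most two arms, so at least two arms have none. Strata are built on teaching status, size and CAP volume, not state. The factorial margins could still balance by chance, but the four-group comparisons cannot. The allocation is not shown.

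**6. What happens to an unseen death.** Both the Data analysis plan and Interim analyses define the rate as deaths divided by included or eligible patients. A patient whose death is not recorded stays in the denominator and is in effect a survivor. Multiple imputation addresses values known to be missing; it does not recover deaths nobody saw.

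**7. Why the size is unknown (illustration only).** None of these inputs is in the documents. Let p be the share of 30-day deaths that occur after discharge, assumed 0.20 to 0.60. Let m be the share of those missed at Florida sites, assumed 0.25 to 1.00.

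- Florida deaths lost: p × m, from 0.20 × 0.25 = 5% to 0.60 × 1.00 = 60%.
- Arm with one Florida hospital among three with equal deaths: p × m / 3, from 1.7% to 20%.
- All trial deaths: from 0.142 × 0.05 = 0.7% to 0.167 × 0.60 = 10%.

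The equal-hospital assumption is itself loose, since Table 2 runs from 110 to 1167 beds. The range is too wide to serve as an estimate.

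**The case against.** **On re-escalation.** ESA is a defined term and the outcome is titled re-escalation to ESA, so the short parenthesis may simply be a list that was not updated. That is plausible, but it does not tell the programmer which list to use, and the literal text gives the wrong answer. A reader might infer that half of re-escalations are lost. The documents do not support this: nine of 18 counts agents, not events, and any restart including a listed agent is still captured. A reader might also infer that the omitted agents are specifically those for resistant pathogens. The article does not say so; it describes the whole class as anti-MRSA/anti-pseudomonal.

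**On mortality.** A reader might infer that Florida deaths are sought only in an Ohio index and are therefore missed. The text does not establish that. The EHR comes first, all hospitals share one EMR system, and the Discussion adds other registries whose content is not described. The analysis models also adjust for prior-year hospital mortality (Data analysis plan). If a Florida site under-records deaths consistently, its prior-year rate is low too and the adjustment absorbs part of the deficit.

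This stands for the modelled comparison, but less so for the safety look. Interim analyses uses the pre-study year as a baseline estimate but describes no adjustment of the comparison between arms. The direction is also open: a Florida hospital in usual care would make the interventions look worse, not safer. Nor does the safety case rest on these two outcomes alone, since ICU transfer, *C. difficile* infection, kidney injury, empyema and readmission are also listed.

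**Conclusion.** The re-escalation definition is wrong as written. It contradicts both the primary ESA definition and the de-escalation outcome listed just before it. Its effect is a one-directional undercount of a secondary outcome, of a size the documents do not allow anyone to compute.

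The mortality point is a risk, not a demonstrated loss. No source equivalent to the Ohio index is named for two of 12 clusters (14.2% of beds), the Outcomes section and the Discussion list different sources, and any shortfall would fall unevenly on the four arms. The exposure is greatest in the six-monthly safety comparison. Neither size nor direction can be stated, so a conclusion that the plan biases the trial towards finding de-escalation safe would go further than the text allows. The abstract's in-hospital label is a separate inconsistency, because the Outcomes section seeks vital status outside the hospital record.

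**What to change.** 1. **Re-escalation list.** Replace the nine-agent parenthesis with the 18-agent list of the primary outcome, or with a reference to it. This is a code-list edit that needs no new data.
2. **Death source.** Ascertain 14- and 30-day deaths from an equivalent source at all 12 hospitals, for example a Florida or national death file alongside the Ohio index, and state that it serves both windows and the safety look. The cost is one additional linkage.
3. **If the linkage is not obtained.** Add a sensitivity analysis of 14- and 30-day mortality restricted to the ten Ohio hospitals. It needs no new data but gives up two clusters.
4. **Keep the fixed windows.** Do not substitute in-hospital death for the cross-arm comparison. It depends on when patients are discharged, and length of stay is itself an outcome that the interventions may change.
5. **Wording.** Make the abstract's 14-day mortality label agree with the Outcomes section, and make the Outcomes section and the Discussion list the same sources. This is a text edit.

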## Statistical methods

### Data analysis plan

The data analysis will be conducted following the intention-to-treat (ITT) principle which includes 3 rules. The first rule establishes the landmark event for entry into the study, which is the randomization of hospitals. All randomized hospitals will be considered enrolled, and data of eligible patients treated by enrolled hospitals will be analyzed. The second rule establishes patient-level data collection, which is independent of treatment assignment. The third rule defines the pre-specified time period for counting study events, which varies for each outcome.

We will follow the order principle of analyses, which states that analyses involving the primary outcome measure must be preceded by analyses of higher-order outcomes when those outcomes are censored. In our study, all-cause death events are censored. To follow the order principle of analyses, we will compare the all-cause mortality incidence rate within the first 30 days of admission across the four treatment groups. Incidence rate is calculated as the number of all-cause deaths divided by the number of included patients and expressed per 1000 (or 10,000 patients) per 30 days of follow-up. We will calculate the incidence-rate difference between the four treatment groups, using the usual care group as the reference. The four treatment arms are rapid testing and de-escalation, rapid testing only, de-escalation only, and usual care (i.e., neither rapid testing nor de-escalation).

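### 72-h de-escalation is not a fair measure of rapid testing because it requires an ESA start, which testing is meant to prevent; re-escalation among de-escalated patients has a similar selection problem for the pharmacist factor

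*Protocol article*

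**What the plan says.** The Outcomes section lists two linked binary secondary outcomes. The first is the proportion of patients whose ESA "are de-escalated within 72 h from admission". The second, followed to 21 days, is the "Proportion of patients whose antibiotics were de-escalated and that were subsequently re-escalated to ESA". Neither names its denominator.

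Three other parts of the article bear on how these outcomes behave:

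- **Who is analysed.** Patients enter on an "admitting diagnosis of pneumonia" (Study recruitment and participant identification; likewise Eligibility criteria). No ESA start is required. Under intention to treat, "data of eligible patients treated by enrolled hospitals will be analyzed" (Data analysis plan).
- **What de-escalation is.** The Pharmacist-led de-escalation section defines it as stopping every anti-MRSA and antipseudomonal agent. A patient who never starts one cannot have the event.
- **What the interventions are meant to do.** The abstract describes "rapid diagnostic assays that can provide accurate results within hours, obviating the need for empiric therapy". Background and rationale says an early diagnosis helps first "by allowing for initial narrow-spectrum therapy", and second by giving confidence to de-escalate. The other factor is "pharmacist-led de-escalation after 48 h for clinically stable patients with negative cultures" (Interventions), so it changes who stops an ESA, not who first starts one.

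**The concern.** By the protocol's own account, rapid testing works partly by preventing ESA starts. A de-escalation outcome cannot credit that route. Over all patients, a prevented start is scored the same as a patient kept on an ESA. Among starters, the denominator is a group formed after randomisation and altered by the intervention, so randomisation no longer protects the comparison.

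The pharmacist factor has a parallel difficulty one step later. It enlarges and changes the group of de-escalated patients, so re-escalation within that group compares unlike patients.

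Two readings are at stake: whether testing reduced early ESA use, and whether de-escalation was safe. The Discussion gives demonstrating that safety as an aim, and re-escalation bears directly on it.

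**Working it through.** The article gives no ESA start rate, share of starts avoided, or de-escalation and re-escalation rates for this trial's patients, so there is no stated figure to reproduce. All counts below are assumptions chosen to show direction.

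**Step 1. 72-h de-escalation and the testing factor.** Per N eligible patients under usual care, let S start an ESA and D be de-escalated by 72 h. Testing avoids a starts, of which x (between 0 and a) would have been de-escalated. Nothing else changes; early deaths and restarts before 72 h are ignored.

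- Over all patients: (D − x)/N against D/N. The change is −x/N, never positive.
- Among starters: (D − x)/(S − a) against D/S. It falls if x/a exceeds D/S, is unchanged if they are equal, and rises if x/a is smaller.
- On an ESA at 72 h, over all patients: [S − D − (a − x)]/N against (S − D)/N. The change is −(a − x)/N, never an increase.

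With N = 1000, S = 400, D = 120 and a = 50, usual care gives 120/1000 = 12.0%, 120/400 = 30.0% and 280/1000 = 28.0%. The starter proportion changes direction at x = 50 × 0.30 = 15.

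| x of the 50 avoided | De-escalated, all patients | De-escalated, starters | On ESA at 72 h, all patients |
|---|---|---|---|
| Usual care | 12.0% | 30.0% | 28.0% |
| 0 | 120/1000 = 12.0% | 120/350 = 34.3% | 230/1000 = 23.0% |
| 10 | 110/1000 = 11.0% | 110/350 = 31.4% | 240/1000 = 24.0% |
| 15 | 105/1000 = 10.5% | 105/350 = 30.0% | 245/1000 = 24.5% |
| 30 | 90/1000 = 9.0% | 90/350 = 25.7% | 260/1000 = 26.0% |
| 50 | 70/1000 = 7.0% | 70/350 = 20.0% | 280/1000 = 28.0% |

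The all-patient directions hold for any inputs. The starter direction depends on case mix.

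**Step 2. Re-escalation and the testing factor.** Per 1000 patients, assume 200 readily de-escalated starters (50% de-escalated, 5% of those re-escalated) and 200 less readily de-escalated starters (20% and 15%). Usual care gives 100 + 40 = 140 de-escalated and 5 + 6 = 11 re-escalated, which is 1.10% of all patients and 11/140 = 7.9% of the de-escalated. Now let testing avoid 25% of starts in the group named:

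- Readily de-escalated only: 9.75 of 115, which is 0.98% of all and 8.5% of the de-escalated.
- Both groups: 8.25 of 105, which is 0.83% and 7.9%.
- Less readily de-escalated only: 9.5 of 130, which is 0.95% and 7.3%.

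Over all patients the proportion falls each time, favouring testing. Among the de-escalated it can go either way.

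**Step 3. Re-escalation and the pharmacist factor.** Keep the same 400 starters and the same re-escalation risk within each group. Add 60 de-escalations, the number that lifts the second group from 20% to 50%: 200 × (0.50 − 0.20) = 60.

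- If all 60 come from the less readily de-escalated group: 11 + 60 × 0.15 = 20 re-escalated of 200 de-escalated, which is 10.0% against 7.9%, and 2.0% of all against 1.10%.
- If all 60 come from the readily de-escalated group: 11 + 60 × 0.05 = 14 of 200, which is 7.0% against 7.9%, and 1.4% of all against 1.10%.

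The conditional proportion moves in either direction although no patient's risk after de-escalation has changed. The all-patient proportion rises because more patients are at risk.

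**The case against.** - **A reader might infer that avoided starts count against testing whichever denominator is used.** The documents do not support that. Among starters the direction is open, and for re-escalation over all patients avoided starts favour testing. The finding that "patients who tested positive with UAT were twice as likely to have their ESA de-escalated by hospital day 3" (Background and rationale) makes it plausible that the avoided starters would be the easier cases, but it is an association and does not establish this. Nor does it follow that testing will look worse overall, since testing may also raise de-escalation among those who do start.
- **The denominator may be fixed in an analysis plan that is not shown.** It may, and a missing denominator alone would be no finding. But neither natural choice makes 72-h de-escalation a fair measure of the testing factor. The planned mixed models and the adjustment for prior-year rates do not undo selection that arises after randomisation.
- **The consequence is limited.** This stands. The two hypotheses on days of ESA rest on the primary outcome, to which an avoided start contributes no ESA days and re-escalation contributes its days. Mortality, ICU transfer, empyema, readmission, kidney injury and *C. difficile* infection carry no condition on ESA use.
- **Re-escalation over all patients is already one natural reading of the text.** This also stands, and it is a valid randomised contrast. It needs reading beside ESA status, because it rises when more patients are de-escalated, and it misses a late first ESA start in a patient who began on narrow therapy.

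**Conclusion.** The point holds for two secondary outcomes. For the testing factor, 72-h de-escalation over all eligible patients can be lowered, and never raised, by avoided ESA starts; in the illustration 12.0% becomes anything from 12.0% down to 7.0%. Among starters the same 50 avoided starts give 20.0% to 34.3% against 30.0%, so the bias has no fixed sign. For the pharmacist factor, re-escalation among de-escalated patients compares groups that the intervention has changed, again with unknown direction.

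The all-patient directions follow from the definitions and need only that testing avoids some starts, as the protocol expects. The sizes are assumptions, because the article gives no figures for them. The primary outcome is unaffected. The change is worth making, but the trial's main conclusion does not depend on it.

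**What to change.** For comparisons between arms:

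1. Replace 72-h de-escalation with receipt of any ESA at 72 h (yes/no) in all eligible patients. Count patients who never started as not on an ESA, and state a rule for death before 72 h, so that early death is not scored as success. A composite of on an ESA or dead is one example.
2. Replace re-escalation with any ESA start or restart after 72 h and within 21 days in patients not on an ESA at 72 h, counted as an event over all eligible patients. This captures late first starts. Report it beside the 72-h status, since an arm with more patients off ESA has more at risk.
3. Keep de-escalation among starters and re-escalation among de-escalated patients as descriptive process measures, labelled as conditional on events after randomisation.

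The cost is a small change of secondary-outcome wording. The dose data, including prescribed doses after discharge, are already extracted for the primary outcome. What is given up is a direct between-arm test of de-escalation as a process, which remains visible in the descriptive tables. The change should be documented before outcomes are compared by arm.
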